### Study Setting

The study is conducted at Amrita School of Ayurveda, Kollam, Kerala, and recruits participants from India only. The institute is a constituent of Amrita Vishwa Vidyapeetham and supports teaching and research. Figure 1 depicts the flowchart of the trial’s methodology.

**Figure 1. F1:**
[figure not shown]
Summary of the methodology. CRF: case report form; CTRI: Clinical Trial Registry-India; IEC: institutional ethics committee; IPD: inpatient department.

### Primary Purpose

The intervention aims to decelerate the process of aging in humans. The date of first enrollment was March 2025, and the target sample size was 53 healthy volunteers. This trial is undertaken as part of a doctoral research project. The trial is ongoing and still recruiting participants. The total trial duration is 3 years.

### Eligibility Criteria

#### Inclusion Criteria

Healthy volunteers of either gender are included if they are aged 35 years to 60 years; are registered in the outpatient department, School of Ayurveda, Amrita Vishwa Vidyapeetham, Amritapuri, India; are willing to take part in the study; have a BMI between 18.5 kg/m^2^ and 25 kg/m^2^, have a stable weight (change <±10%) for 3 months immediately prior to the study; have *madhyama koshta* (medium nature of bowel evacuation, as assessed using a questionnaire); and are *vamanarha* (eligible for therapeutic emesis) and *virechanarha* (eligible for therapeutic purgation).

#### Exclusion Criteria

Indviduals were excluded for the following reasons: pregnancy or currently breastfeeding; addicted and unwilling to abstain from tobacco, alcohol, or recreational drugs; history of eating disorders; history of an acute or chronic inflammatory disorder; use of antidepressants or hormone replacement therapy; current diagnosis of posttraumatic stress disorder; unwilling to abstain from rich sources of resveratrol such as antioxidants including vitamin supplements, daily vitamins, resveratrol, minerals, dry grapes, blue berry, peanut butter, dark chocolate, and soy for the duration of study; unwilling to eat only study-provided food during the preconditioning and intervention periods; unstable weight (change >–10%) in the 3 months immediately prior to the study; and food allergies and dietary restrictions.

Those who are unwilling to eat only study-provided food during pre-conditioning and intervention periods.

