**Methods:**

The study was prospectively registered in the Clinical Trial Registry-India (CTRI; CTRI/2024/02/062176), uses a pre-posttest study design, and includes 53 participants 35 years to 65 years old. The study is exploratory and lacks a control group. Those with a BMI between 18.5 kg/m^2^ and 25 kg/m^2^, with stable weight for 3 months immediately prior to the study, with *madhyama koshta* (medium nature of bowel evacuation, as assessed using aquestionnaire), who are *Vamanarha* (eligible for therapeutic emesis) and *Virechanarha* (eligible for therapeutic purgation), and who do not meet the exclusion criteria will be included in the study. The interventions include emesis in the spring and purgation in the autumn season, preceded by *Snehana* (oleation) and *Swedana* (fomentation) and followed by the *Samsarjana karma* (specialized menu of diets) depending on the measurement of purification. Trial duration will range from 18 days to 20 days for each participant, and the total study duration will be 3 years. The serum levels of MDA, SOD, and telomerase activity will be measured on day 0 and on the next day following completion of the *Samsarjana karma* (18th-20th day). Continuous variables for primary biological endpoints including serum MDA, T-SOD, and telomerase activity will be evaluated using paired-samples *t* tests or Wilcoxon signed-rank tests, with potential missing data managed under a missing completely at random assumption using available case analysis (pairwise deletion) cross-verified by a conservative baseline observation carried forward (BOCF) sensitivity test. The effect size will be also determined.

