### Concomitant Care

The study includes only healthy volunteers; therefore, no concomitant care is needed. If any adverse events occur, they will be managed accordingly. Participants are strictly prohibited from self-administering any over-the-counter antacids, antiemetics, antidiarrheals, or conventional laxatives during the trial, as these would confound the assessment of the purification procedures. Enrolling in external physical therapies, attending commercial spa treatments, or initiating new dietary supplements outside the protocol are also restricted.

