### Limitations

Placebos for procedures like *Vamana* and *Virechana* are challenging to include; therefore, this study does not include a control group. However, the resulting single-group study design raises concerns about internal validity.

In addition, this exploratory pilot trial lacks a concurrent, untreated parallel control group. Since this study operates as an investigator-initiated doctoral project embedded within a real-world clinical service, introducing an untreated healthy cohort was operationally and ethically unfeasible, as all recruited individuals are actively seeking immediate wellness interventions. To mitigate this constraint and maximize data validity, each participant serves as their own internal longitudinal control through structured pre- and postintervention paired comparisons. Furthermore, potential lifestyle and environmental confounding variables are strictly controlled by housing all 53 participants within an identical inpatient ward environment throughout the active study timeline.

We acknowledge that serum MDA and T-SOD are short-term surrogate markers of oxidative stress, not direct proof of delayed aging. In this protocol, *Śodhana* represents a complete therapeutic process including *Pūrvakarma* (internal oleation), *Pradhāna Karma* (*Vamana* or *Virechana*), and *Saṃsarjana Krama*. Therefore, acute changes in MDA and T-SOD reflect the immediate metabolic shifts of this entire multiphase cycle rather than long-term aging changes. To address this limitation, we paired these dynamic redox markers with telomerase activity. This allows us to explore whether the intense physiological “reset” caused by the complete *Śodhana* sequence correlates with any stabilizing effects on a deeper, genetic marker of cellular longevity.

The sample size calculation was also pragmatic rather than inferential. The exploratory nature of the study warrants a focus on feasibility of the protocol rather than to test the hypothesis.

The recruitment is seasonal and consecutive. Therefore, differences in environmental factors, including the climate and diet, as well as baseline biological rhythms between the 2 cohorts may act as potential modifiers for biomarker levels.

Although other biomarkers, including an interleukin panel and the microbiome, are available, we included only a limited number of biomarkers for our healthy volunteers due to financial constraints.

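### Current users of tobacco, alcohol, drugs or antioxidants can enrol without abstaining before the day-0 sample, so any cessation effect is mixed into the uncontrolled pre-post change

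*Protocol article*

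**What the plan says.** Two exclusion criteria concern exposures that plausibly bear on the biomarkers.

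- **Tobacco, alcohol, drugs** (Exclusion Criteria): those "addicted and unwilling to abstain from tobacco, alcohol, or recreational drugs" are excluded. No abstention period is given.
- **Antioxidants and supplements** (Exclusion Criteria): those "unwilling to abstain from rich sources of resveratrol such as antioxidants including vitamin supplements" and a list of foods ending "dark chocolate, and soy for the duration of study" are excluded. The period is stated for this item only.

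On timing, the Abstract (Methods) has the biomarkers "measured on day 0 and on the next day following completion of the" post-procedure diet, and says "Trial duration will range from 18 days to 20 days for each participant".

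The Trial Estimand section compares each participant's pre-intervention state with the post-intervention state. There is no control group. The Interventions section declares diet, hydration, physical exertion and sleep to be components of the therapeutic package; stopping tobacco, alcohol, drugs or supplements is not on that list. Concomitant Care adds that "initiating new dietary supplements outside the protocol are also restricted". The regression in Statistical Measures uses baseline biomarker, age, sex and BMI. The Limitations section states that "potential lifestyle and environmental confounding variables are strictly controlled by housing all 53 participants within an identical inpatient ward environment" during the active study.

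**The concern.** A criterion that excludes only the unwilling admits the willing user. If that person's first sample reflects habitual exposure and the second follows almost three weeks of supervised abstinence, the within-person change contains two things: the procedure and the cessation. The trial's only answer is that change.

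The protocol's own reasoning makes the point relevant. It restricts antioxidants, which presupposes that they matter for these endpoints. Its Discussion also argues that 21 to 30 days of altered behaviour (fasting, running training) is enough to move blood oxidative stress markers. On that argument, 18 to 20 days without tobacco, alcohol or antioxidants might move them too.

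The direction may differ by exposure. As an assumption, stopping tobacco or alcohol would favour the hypothesised change and stopping antioxidants would oppose it. Either shift would be credited to the procedure or would mask its effect.

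**Working it through.** **1. Does any preparatory phase act as a washout before day 0?** Take the longest durations in the Interventions section.

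- Vamana: Trikatu 5–7 days, ghee 5–7, special diet 1, procedure 1, graduated diet 1–3. Total 13–19 days.
- If day 0 came after the Trikatu phase, at most 7 + 1 + 1 + 3 = 12 days would remain, so the next-day sample would fall by about day 13.
- Virechana on the same reading: at most 7 + 2 + 1 + 3 = 13 days, so about day 14.

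Neither reaches the stated day 18–20. Day 0 therefore precedes the preparation. The preconditioning period named in the Exclusion Criteria concerns study-provided food and is not defined as a pre-baseline run-in. No section requires abstention before day 0.

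**2. Does the ward hold these exposures constant?** Inpatient housing applies during the active study. For a non-user, exposure is nil at both samples. For a recent user, it is habitual before the first sample and stopped before the second. For that person the ward produces the change; it does not control it.

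**3. Can the planned analysis remove it?** There is no comparison group and no exposure covariate, and cessation is not declared part of the treatment condition. It cannot.

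**4. The plan's own power figure.** Two-sided paired t test, n = 53, d = 0.395, α = .05, noncentral t: power 0.806. This reproduces the stated 80%, and the present point does not alter it.

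**5. Illustrative size.** The documents give neither the share of users nor a cessation effect, so these are assumptions. Let the procedure have no effect, and let a share f of participants shift by s, in SDs of the non-user change score, all in one direction.

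- Mean shift = f·s
- SD = √(1 + f(1 − f)s²)
- Apparent d = f·s / SD
- Noncentrality = d·√53, with 52 df

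For f = 0.2, s = 1: mean shift 0.20, SD = √1.16 = 1.077, d = 0.186.

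The Primary Outcome section requires P<.05 together with a moderate to large Cohen d, and Statistical Measures sets medium at 0.5. With n = 53, an observed d of 0.5 corresponds to t = 0.5·√53 = 3.64, against a critical value of 2.007 for P<.05.

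| f | s | apparent d | P<.05 | observed d ≥ 0.5, in the direction of the shift |
|---|---|---|---|---|
| 10% | 0.5 | 0.049 | 6.4% | 0.1% |
| 20% | 1.0 | 0.186 | 26.4% | 1.6% |
| 30% | 1.0 | 0.273 | 49.6% | 6.1% |
| 50% | 0.8 | 0.371 | 75.6% | 19.3% |

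The last row is an extreme case. The mean change is biased by f·s in every row, whichever success rule is used.

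**The case against.** The strongest reply is that the size is unknown and the limitation is partly disclosed. The trial calls itself hypothesis-generating. The Limitations section concedes that a single group weakens internal validity and attributes changes to the whole multiphase cycle. Future Directions says a control arm is needed to separate the procedure from caloric restriction. Diet is declared part of the package, which reasonably covers the listed foods. All of this stands. It leaves tobacco, alcohol, drugs and supplements, which no section acknowledges and which the strictly-controlled sentence implicitly denies.

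Four stronger readings are tempting, and the documents do not support them.

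- A reader might infer that cessation alone could produce a declared success up to half the time. That counts P<.05 only. Adding the effect-size condition brings the 10%–30% scenarios down to about 0.1%–6%. All scenarios also assume one direction, whereas in a mixed cohort opposing shifts would partly cancel.
- A reader might take the study-long abstention period to cover tobacco, alcohol and drugs. It is attached only to the antioxidant item. The other item states no period and, read literally, excludes only people who are both addicted and unwilling.
- A reader might see a contradiction between Concomitant Care, which bars starting supplements, and the Exclusion Criteria, which deal with existing use. The two rules are complementary; neither permits continued use.
- A reader might conclude that a fixed washout must now become an eligibility rule. The documents give no basis for any particular interval. The 27 participants reported as of April 4, 2025 are all in the Vamana cohort, so a rule applied only to later recruits would largely coincide with cohort. It would confound the planned Vamana-versus-Virechana comparison and mix two baseline definitions in the pooled mean.

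**Conclusion.** The point holds as a design weakness of unknown size. Willing current users are eligible, no abstention before day 0 is required, and any resulting shift in MDA, SOD or telomerase activity cannot be told apart from the procedure's effect. The Limitations sentence on strict control is wrong for these exposures.

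The conclusion on separability rests on the text alone. The magnitude rests on assumed prevalence, an assumed effect size and a single direction of shift: negligible if few users enrol, material for the mean change if many do. The documents do not establish that a false declaration of success is likely.

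**What to change.** 1. Record recent tobacco, alcohol, recreational drug and antioxidant or supplement use at day 0 for every participant, and retrospectively for those already enrolled. The existing history names medication use explicitly but not these exposures.
2. Report the primary MDA and SOD mean changes with and without recent users. Add recent use to the regression in Statistical Measures if numbers allow.
3. State when abstention must begin relative to the day-0 sample, or declare cessation part of the treatment condition in the estimand.
4. Amend the Limitations sentence so that it does not claim control of exposures that change after baseline.

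Any pre-baseline interval is for the sponsor to set. If one is introduced mid-trial, the between-cohort comparison must note that it largely coincides with cohort.

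The cost is a few history items and one sensitivity analysis, with possible recall error for those already enrolled. The analysis without recent users is less precise. If 20% were recent users, about 42 pairs would remain (53 × 0.8 = 42.4), and power at d = 0.395 would fall from 0.81 to 0.71, so it should stand as a sensitivity analysis beside the full-cohort result.

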### Evaluation of Healthy Volunteers

All the participants will be evaluated for healthy status through a clinical assessment and baseline laboratory screening.

The clinical assessment consists of a complete history-taking including usage of any current and concomittant medication, and a thorough systemic clinical examination including monitoring of vital signs will be performed at baseline. Any clinical findings deviating from the defined status of healthy volunteers will result in exclusion of the candidate.

Baseline laboratory screening includes a complete blood count (CBC) with erythrocyte sedimentation rate, lipid profile, blood glucose levels, renal function test, liver function test, thyroid function test, and urine routine examination to rule out any existing co-morbidity. The results of all these tests must fall within the standard physiological reference range for a participant to be includeds in the study.

### Strategies for Enrollment Promotion and Recruitment Feasibility

This research study is directly embedded within a long-standing, highly popular seasonal clinical service at our institute. Hence, external promotional advertisements, public campaigns, or medical record prescreening are not required to achieve our target sample size. The institute possesses an organic, highly motivated pool of community members who voluntarily register for the *Vasantha Vamana* and *Sharad Virechana* health maintenance sessions on their own initiative each year. To promote adequate enrollment and successfully secure our cohort of 53 healthy participants from this existing pipeline, our strategy focuses on systematic opportunistic screening and minimizing volunteer burden.

### Interventions

#### *Vamana* (Therapeutic Emesis)

##### *Poorvakarma* (Preoperative Procedure)

*Pachana* (carminative)–*Deepana* (digestive) with *Trikatu choorna* (herbal powder containing *Terminalia chebula, Terminalia bellarica,* and *Embelica officinalis*) is administered until pakwa mala lakshanas (symptoms indicative of proper digestion) are observed.

Recruited participants receive 3 gm *Trikatu choorna* with one-half glass of water twice daily after food for a period of 5 days to 7 days.

*Snehapana* (oleation) with *Moorchita ghruta* (ghee processed with herbs) is administered until *samyak snigdha lakshana* (symptoms indicative of proper oleation) are observed (using a validated tool).

Following the observation of *pakwa mala lakshana*, the participants will be advised to drink ghee. The ghee will be administered in increasing doses (depending on digestive capacity) starting at 30 mL. The time of administration will be around 7 AM. Upon consuming the ghee, the participant should sip warm water and wait until the ghee is digested properly (observed by the appearance of hunger and clear belching devoid of taste of the ghee). The same process is repeated for 5 days to 7 days.

For *Kaphotkleshakara Ahara*, once we observe the proper signs of oleation, idli (a South Indian preparation) with sugar and milk (breakfast), rice with curd (lunch), *tila* laddu (sesame balls)/*masha* (sweet pudding made of blackgram) *payasam* (evening snack), and rice and milk (dinner), all in quantities per the digestive capacity of the individual, will be administered on the next day.

*Sarvanga abhyanga* (whole body massage) with *moorchita taila* (oil processed with herbs) followed by *Bashpa sweda* (fomentation) will also be performed on the same day.

##### *Pradhana Karma* (Main Procedure)

*Vamana* will be conducted using *Madanaphala yoga* (drug prepared from *Randia dumetorum*) on the next day preceded by *Sarvanga abhyanga* (whole body massage) with *moorchita taila* followed by *Bashpa sweda* (fomentation) in the morning around 6:30 AM.

For *paschat karma* (the postoperative procedure), *Gandusha* (gargling), *Dhoomapana* (inhaling medicated fumes), and washing the lower part of the body with warm water will be performed.

*Samsarjana krama* (modified dietic regimen) will then be advised based on *sudhi lakshana* (signs and symptoms suggestive of a proper therapeutic emesis) for 1, 2, or 3 days.

### *Virechana* (Therapeutic Purgation)

#### *Poorvakarma* (Preoperative Procedure)

*Pachana* (carminative)–*Deepana* (digestive) with *Trikatu choorna* is administered until *pakwa mala lakshana* are observed.

Recruited participants receive 3 gm of *Trikatu choorna* with one-half glass of water twice daily after food for a period of 5 days to 7 days.

*Snehapana* (oleation) with *Moorchita ghruta* is administered until *samyak snigdha lakshana* are observed (using a validated tool).

After observation of *pakwa mala lakshana*, the participants will be advised to drink ghee. The ghee will be administered in increasing doses (depending on digestive capacity) starting at 30 mL. The time of administration will be around 7 AM. Upon consuming the ghee, the participant should sip warm water and wait until the ghee is digested properly (observed by appearance of hunger and clear belching devoid of the taste of the ghee). This process is repeated for 5 days to 7 days.

*Sarvanga abhyanga* (whole body massage) with *Moorchita taila* followed by *Bashpa sweda* (fomentation) will be administered for 2 days prior to virechana and on the day of *virechana*.

#### *Pradhana Karma* (Main Procedure)

*Virechana* will be completed using *Trivrit Lehya* (drug prepared from *Operculina turperthum*) at around 7 AM.

For *paschat karma* (the postoperative procedure), after attaining hunger and when the participant ceases to feel the urge for defecation, he/she will be allowed to take a bath in warm water.

Based on the *sudhi lakshana* (signs and symptoms suggestive of a proper purgation), the participant will be advised to follow *samsarjana* (modified dietic regimen) for 1, 2, or 3 days.

The participants will be admitted to the hospital for the duration of the trial. The administered diet will be uniform for all participants. Hydration will also be monitored. Participants are restrained from doing strenuous physical activity throughout the intervention. They are also advised to sleep for a strict 6 hours to 8 hours. The strictly enforced controls on diet, hydration, physical exertion, and sleep are not external protocol restrictions but standardized, fundamental therapeutic components (*Ahara* and *Vihara*) inherent to the classical *Śodhana* (Panchakarma) and *Samsarjana Krama* (graduated postdetox dietary timeline) intervention package. These parameters are operationally deployed within an institutional setting to ensure uniform clinical delivery.

### Intervention Provider Qualifications and Quality Control

The trial will be monitored and supervised by the principal investigator, who holds a Doctor of Medicine (MD) in Kayachikitsa (Ayurvedic Internal Medicine) and possesses 10 years of postgraduate clinical, research, and academic experience. The *Poorvakarma* procedures (including *Abhyanga* and *Sweda*) will be performed by following the institutional standard operating procedures (SOPs) by institutional Panchakarma therapists formally trained and employed at our institute. To ensure intervention fidelity and minimize practitioner-induced variability, all therapists will complete a mandatory, protocol-specific practical alignment session led by the principal investigator. Moreover, the investigator will audit the treatment sessions to ensure strict compliance with the protocol. As this is an exploratory study, a secondary objective is to evaluate the feasibility of the protocol. Intervention fidelity will be maintained through adherence to written institutional SOPs overseen by the principal investigator.

### Participant Adherence

The study is conducted under direct observation of the investigators. The participants will remain inpatients in the hospital (study setting). Every dose of *Snehapana*, the medicines to induce *Vamana* and *Virechana*, and all rescue medications, if any, will be administered directly under the visual supervision of the institutional nursing staff and verified by the investigator. Hence, for this trial, compliance shall be defined as 100% doses taken, excluding circumstances that will result in withdrawal of participants. Participant adherence rates will be descriptively tracked daily by the team to evaluate the tolerability of the purification phases. This tracking includes monitoring compliance with the daily titrated *Snehapana* volumes, *sodhna* procedure, and the *Samsarjana Krama*. The collected adherence data will directly inform the feasibility design and sample size calculations of future definitive trials.

To address the inherent adherence challenges of complex interventions like *Vamana* therapy, participant retention will be secured through structured preprocedural patient education and continuous clinical oversight. Prior to the procedure, participants will receive thorough education regarding the operational steps and safety parameters of *Vamana* to manage expectations and reduce procedural anxiety. Furthermore, the entire therapy will be executed under close clinical supervision; the principal investigator and trained nursing staff will remain at the bedside to monitor vitals, provide reassurance, and ensure strict protocol compliance.

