#### Secondary Objective

The secondary objective is to determine the change in serum telomerase activity from baseline to postintervention.

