### Participant Retention and Discontinuation Protocols

Participant retention is optimized through the fully managed inpatient environment. This trial tracks an existing clinical service where healthy volunteers are admitted as full hospital inpatients for the duration of the *Śodhana* therapy; therefore, typical outpatient compliance barriers like travel issues, appointments being forgotten, or accidental dietary deviations are naturally eliminated.

For participants who voluntarily withdraw or deviate from the intervention protocols after formal enrollment, active procedures are immediately halted to protect participant autonomy and safety. Unless written consent is completely revoked, the specific outcome data collected and retained for these individuals will consist of baseline serum MDA, T-SOD, and telomerase levels, along with a documented record of the exact chronological point and clinical reason for the protocol deviation or study exit. The reasons for nonadherence and nonretention will be recorded on the CRF. All recorded reasons will be compiled into a standardized trial flow diagram and fully disclosed in the final manuscript publication.

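### The compliance definition sets aside anyone who withdraws, so it gives close to 100% by construction and cannot serve as the feasibility measure

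*Protocol article*

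**What the plan says.** Participant Adherence describes dosing under direct supervision and concludes from it that "compliance shall be defined as 100% doses taken, excluding circumstances that will result in withdrawal of participants". The same paragraph then says: "Participant adherence rates will be descriptively tracked daily by the team to evaluate the tolerability of the purification phases". That tracking covers the ghee volumes, the purification procedure and the graduated diet. The paragraph ends with the intended use: "The collected adherence data will directly inform the feasibility design and sample size calculations of future definitive trials".

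Participant Retention and Discontinuation Protocols adds: "For participants who voluntarily withdraw or deviate from the intervention protocols after formal enrollment, active procedures are immediately halted". It also requires the timing and reason of each deviation or exit to be documented, and the reasons to be published in a flow diagram.

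On objectives, Intervention Provider Qualifications and Quality Control says that "a secondary objective is to evaluate the feasibility of the protocol". The Secondary Objective section itself lists only telomerase: "The secondary objective is to determine the change in serum telomerase activity from baseline to postintervention". The Limitations section says that the exploratory design calls for attention to feasibility rather than to hypothesis testing. Core Outcome Set and Summary Measures adds the proportion of participants with rescue events as a feasibility and safety outcome.

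**The concern.** A compliance rate is informative only if participants who fail to comply stay in the denominator. Here the definition excludes circumstances that end in withdrawal, and the retention section turns deviation into a halt of procedures. A participant who refuses a dose or stops during the main procedure is therefore likely to fall under the exclusion instead of being counted as non-compliant. Those who remain took every dose.

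This matters more than it would in a purely confirmatory study, because feasibility is a declared purpose and adherence is named as an input to the design and size of later trials. A figure near 100% that comes from the definition could be mistaken for evidence that the full sequence is well tolerated by healthy volunteers.

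**Working it through.** **Step 1: the rules side by side.**
- Definition (Participant Adherence): all doses taken, with withdrawal circumstances left out.
- Consequence of deviating (Participant Retention and Discontinuation Protocols): "active procedures are immediately halted to protect participant autonomy and safety".
- Combined: let N be the participants who start and k those who withdraw or are halted. Compliance as defined is (N − k)/(N − k) = 100% for every k. The result is close to 100% rather than exactly 100%, because a missed dose that leads to neither withdrawal nor a halt would still count. The definition alone does not say that a person who misses a dose is removed; that step comes from the retention section.

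**Step 2: what the plan gives to compare with.** The article states no compliance rate, so there is none to reproduce. The relevant figures are the sample size of 53 and the 20% dropout (Sample Size), and expected missing data below 5% (Statistical Handling of Missing Data). The 53 reproduces: 1.96² × 0.5 × 0.5 / 0.15² = 42.68, and 42.68 / 0.80 = 53.4.

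**Step 3: rate over all starters, (N − k)/N.** The values of k are assumptions. Intervals are Wilson 95% CIs.

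| Lost, k | As defined | All starters | 95% CI | Gap (percentage points) |
|---|---|---|---|---|
| 3 of 53 | 50/50 = 100% | 50/53 = 94.3% | 84.6% to 98.1% | 5.7 |
| 11 of 53 | 42/42 = 100% | 42/53 = 79.2% | 66.5% to 88.0% | 20.8 |

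The second row is the protocol's own dropout: 20% of 53 is 10.6, rounded to 11. The first row is 3/53 = 5.7%, slightly above the missing-data rate that the plan expects. Exact (Clopper-Pearson) intervals are similar: 84.3% to 98.8% and 65.9% to 89.2%.

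**Step 4: the other reading of 53.** Expected Completion ends the trial once 53 participants have completed. With 20% lost, 53 / 0.80 = 66.25, so about 67 would start, and 53/67 = 79.1% (exact 95% CI 67.4% to 88.1%). The conclusion is the same.

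**The case against.** The strongest reply is that compliance and adherence are two different things in this section. The compliance sentence comes first. The next sentence introduces daily adherence rates by component, and the sentence about future trials follows that one. On this reading the later trial would rest on the daily rates, which can fall. Non-adherence is also recorded elsewhere: the retention section documents the time and reason of each exit and publishes the reasons, Rescue Medications has gastrointestinal symptoms, dizziness and inadequate or excessive purification entered on the CRF, and Core Outcome Set and Summary Measures reports rescue events. Intolerance during oleation leads first to observation and rehydration, not to a stated withdrawal. No biomarker estimate or test depends on the compliance figure.

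Most of this stands, and it limits the point in two ways. A reader might infer that the feasibility objective is left unanswered. The documents do not support that, because a completion rate could be rebuilt from the exit records. A reader might also infer that the next trial would necessarily be planned on a figure that cannot fall. That goes too far as well, since the daily rates may be what is meant.

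The reply does not rescue the defined measure. The daily tracking is itself described as monitoring compliance, the term just defined with the exclusion, and nothing says that its denominator differs. The definition could also be read as a 100% threshold with withdrawals exempted. That reading still keeps withdrawals from counting as non-compliance.

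**Conclusion.** The point holds in a limited form. Read with the retention section, the compliance definition yields a figure close to 100% by construction. It tells nothing about feasibility and conflicts with the stated use of adherence data for feasibility and future sample sizes. The other planned records still inform feasibility, but they leave the defined measure as it is.

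The overstatement would be about 6 percentage points with 3 of 53 lost and about 21 with 11 of 53 lost. These sizes rest on assumed event counts, on participants who deviate being halted as the retention section says, and on compliance being reported as defined. The absence of detailed feasibility criteria from the article is not part of the point, since the full protocol may hold them.

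**What to change.** In Participant Adherence:
1. Delete the clause that excludes circumstances leading to withdrawal.
2. Report adherence over all participants who receive the first study dose. Count withdrawn or halted participants as not fully adherent, give a 95% CI, and show the reasons separately.
3. Report a missing post-intervention sample that has a laboratory or logistical cause apart from non-adherence, since it says nothing about whether the participant tolerated the procedures.
4. State that the daily component rates use this same denominator, and that this figure is the one carried into planning the next trial.

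The cost is wording, plus a less favourable reported adherence. Daily tracking and exit reasons are already planned, and the article describes recruitment as ongoing and analysis as pending, so the change can be made before analysis. No dose, halting rule or biomarker analysis changes.
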